### Interventions

Eligible participants will be randomly assigned to either the XBP group or the placebo group. If XBP was used prior to randomization, a 2-week drug washout period was implemented to avoid any potential complications of XBP. All participants will receive conventional basic treatment.

Patients in the experimental group will receive XBP (approval number: Z44021843, 4 pills at 60 mg each, po, three times a day). Patients in the control group will receive XBP placebo (4 pills at 60 mg, po, three times a day). The appearance, taste and weight of the placebo will be the same as those of the XBP test drug. Both XBP and placebo will be manufactured by Guangdong Xinbao Pharmaceutical Technology Co., Ltd. And all drugs should meet the requirements of the Chinese National Drug Manufacturing Code. The total treatment course will be 12 weeks.

Conventional basic treatment was provided in accordance with the 2018 Chinese Heart Failure Diagnosis and Treatment Guidelines published by the Chinese Society of Cardiovascular Diseases (Group et al., 2018), including use of ACEIs, ARBs, ARNIs, diuretics, β-blockers and other drugs to reduce cardiac load and enhance myocardial contractility. Each patient should continue to receive the same type and dose of drugs in the conventional basic treatment protocol as that of before enrollment during the treatment period of the trial. No further adjustments can be made during the entire treatment period. If the condition requires a medication adjustment, it should be recorded in the case report form, and investigators should record the combined endpoints and adverse events that occur in patients who receive an increased or decreased dose of medication or type of a different medication.

Concomitant therapy for comorbidities (e.g., hypertension, angina pectoris, hyperlipidemia, and other chronic conditions) will be allowed during the trial. Investigators should accurately document concomitant medications and maintain dose stability for the duration of the trial. Patients will adhere to heart-healthy diet during the trial, such as a low-salt diet and moderate water intake, in addition to receiving counseling on appropriate lifestyle improvements such as weight monitoring, physical activity, smoking cessation, and alcohol cessation. Adherence will be evaluated by complete documentation of drug distribution and retrieval, and subjects will be judged to be following the protocol if the actual amount of drug taken is within 80%–120% of the applied drug amount.

## Outcomes

### Primary outcomes

Details of the observational items and the time window for data collection are shown in Table 2. The primary outcome will be the proportion change of patients with a decrease of more than 30% in serum NT-proBNP after treatment.

**TABLE 2 T2:** Study procedure table.

Study phase time	Baseline period	Intervention period			Follow-up
	Visit 1	Visit 2	Visit 3	Visit 4	Visit 5
	−7 to 0 days	4 weeks	8 weeks	12 weeks	24 weeks
Data collection at baseline					
Inclusion/exclusion criteria	×				
Informed consent	×				
Demographic data	×				
Obtain the central random number	×				
Previous history, medical history, and allergies	×				
Efficiency evaluation					
NT-proBNP	×	×	×	×	×
Echocardiographic parameters	×	×	×	×	×
NYHA class	×	×	×	×	×
6MWT	×	×	×	×	×
MLHFQ score	×	×	×	×	×
TCM symptom scores	×	×	×	×	×
Clinical-endpoint events	×	×	×	×	×
Safety evaluation					
Vital signs	×	×	×	×	×
Physical examination	×	×	×	×	×
Blood routine	×	×	×	×	×
Urine routine	×	×	×	×	×
ECG	×	×	×	×	×
Blood biochemistry	×	×	×	×	×
Chest radiograph	×			×	×
Other work					
Dispense drug	×	×	×	×	
Recovery and record of study drug		×	×	×	
Record AEs		×	×	×	
Complications due to medications		×	×	×	
Evaluate compliance		×	×	×	×

NYHA, New York heart association; 6MWT, 6-min walk distance test; MLHFQ, Minnesota living with heart failure questionnaire; ECG, electrocardiogram; AE, adverse event; “x” represents the need for implementation at this point in time.

### Secondary outcome indicators

1) cardiac function classification (NYHA) (Yancy et al., 2013); 2) the 6-minute walking distance test (6MWT) (Ingle et al., 2005); 3) the Minnesota Living with Heart Failure Questionnaire score (Fitz et al., 2021); 4) the rate of endpoint events (acute exacerbation rehospitalization of CHF, cardiac death and all-cause death, *etc.*); 5) serum NT-proBNP level; 6) cardiac function indicators, such as the left ventricular ejection fraction (LVEF), the left ventricular end-diastolic diameter (LVEDD), and the left ventricular end-systolic diameter (LVESD); and 7) TCM symptom scores (Supplementary material 1) will be used to quantify the symptoms. Differences in TCM symptom scores between groups at baseline and week 4, week 8, week 12 and week 24 post-treatment will be compared and differences between groups will be calculated. The scoring process will be carried out independently by two chief TCM physicians with more than 5 years of medical experience, with any discrepancies being resolved through consultation. The comprehensive efficacy criteria were as follows: 1) ineffective: no significant improvement or even worsening of symptoms and signs, and a reduction in symptom score <30%; 2) effective: improvement of symptoms and signs, and a reduction in symptom score ≥30%; 3) significant effect: significant improvement of symptoms and signs, and a reduction of syndrome score ≥70%. TCM symptom scores = [(posttherapy score - pretherapy score)/pretherapy score]  ×  100%. Outcome indicators will be collected at week 4, 8, 12 and 24 after inclusion in the study.

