## Abstract

**Introduction:** Chronic heart failure (CHF) is a common cardiovascular disease. In China, Xinbao pill (XBP) is widely used as an adjuvant therapy for CHF. However, there is still a lack of high-quality clinical evidence. We designed this multicenter, randomized, double-blind, placebo-controlled trial to critically evaluate the efficacy and safety of XBP as an adjuvant treatment for patients with CHF.

**Methods and analysis:** We will recruit 284 patients with a clinical diagnosis of “heart-kidney yang deficiency syndrome” CHF receiving treatment in six hospitals in China. Patients will be randomly assigned, in a 1:1 ratio, to the treatment or control group using a central randomization system. All patients will receive conventional drug therapy for heart failure combined XBP (Guangdong Xinbao Pharmaceutical Co., Ltd., Guangdong, China) or a placebo. Study physicians, subjects, outcome assessors, and statisticians will be blinded to the group assignment. The primary outcome will be the change in the proportion of patients who show a decrease in serum NT-proBNP of more than 30% after treatment. Secondary outcomes are NYHA class, 6-minute walk distance test, Minnesota Quality of Life Scale score, endpoint events, serum NT-proBNP, echocardiographic parameters, and traditional Chinese medicine (TCM) symptom score. Adverse events will be monitored throughout the trial. Data will be analyzed according to a predetermined statistical analysis plan.

**Discussion:** The results of this study will provide solid evidence of the safety and efficacy of XBP as an alternative and complementary treatment measure for patients with CHF.

**Clinical Trial Registration:** Chinese Clinical Trial Registration Center (ChiCTR2000038492).

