### Termination criteria

The clinical trial will be terminated if any of the following occur during the course of the trial.1) discontinuation of treatment at any time; 2) an allergic reaction clearly associated with the study drug; 3) an adverse sign or symptom (for example, vomiting, diarrhea, dizziness and headache, weakness, *etc.*) clearly associated with the study drug, or an abnormal test result that, in the judgment of the investigator, warrants discontinuation of the study; 4) pregnancy in a woman; 5) an endpoint event. When a trial is discontinued, all trial records should be retained for review.

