### Withdrawal criteria

All screened and qualified subjects for entry into the trial who complete the informed consent form will not be affected by their subsequent treatment, regardless of when or why they withdraw from the study. Patients have the right to withdraw from the study at any time and for any reason, but every effort should be made to avoid unnecessary patient withdrawals and to complete follow-up visits whenever possible to collect data for analysis of efficacy and safety. However, when a patient decides to withdraw, the investigator should contact the patient or their responsible relative by telephone or personal visit and confirm the reason for withdrawal if possible. The investigator should retrieve the remaining medication at the time of withdrawal, perform complete a final assessment, complete a case report if possible, explain the reason for withdrawal, and follow up on the occurrence of the endpoint event in the withdrawing patient. If the patient withdraws for reason of an adverse event, it should be documented in the complete case report form (CRF).

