### Blinding

Blinding codes will be made after the randomization operation. This process will be performed by a special person, and the sequence number of the subject, the corresponding random numbers and the grouping result (i.e., subjects are assigned to either the test or control group) will be the primary blinding base; then the two groups will be blinded to the medication, which will be the secondary blinding base, and the drug number of each subject will be randomly prepared in order, and all operations will be recorded and maintained. All study personnel, participants, physicians, medication administrators, and dispensing nurses will be unaware of the group and treatment type until the study is completed. Unblinding occurred if a participant have a serious adverse event during the course of the study or require emergency care in an emergency situation. Once unblinded, the participant will be withdrawn from the study and the investigator will report the reason to the examiner within 24 h.

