### Adverse events

Adverse events will be monitored continuously during treatment and follow-up. Adverse events occur during the course of the study, especially those related to the trial drug, will be followed until the patient’s condition returns to baseline status or stabilizes. If the patient’s condition does not return to baseline or stabilize after follow-up, a note should be documented in the CRF. Any serious adverse events during the clinical trial will be reported to clinical trial supervisor, principal investigator, and drug manufacturer within 24 h. Moreover, the investigator will fill out a serious adverse reaction form to record the time of occurrence, severity, duration, measures taken and regression of the serious adverse event. The investigator will also make a judgment on whether the abnormal laboratory results are clinically significant and provide possible explanations. Abnormal laboratory results resulting from an adverse event that has already been reported should also be recorded as an adverse event. Clinically significant abnormal laboratory tests that meet one or more of the following conditions should be recorded as a separate diagnosis on the adverse events page of the CRF (excluding abnormal laboratory results resulting from an adverse event that has already been reported): 1) if accompanied by clinical symptoms; 2) if a change in the study medication has occurred; or 3) if a change in the combination medication and/or other therapeutic measures is required.

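### The stated unblinding rule conflicts with the blinding claims and lets the cause of a heart-failure readmission be judged by someone who knows the arm

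*Protocol article*

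**What the plan says.** All references are to the protocol article.

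- **Who is blinded.** The Abstract says: "Study physicians, subjects, outcome assessors, and statisticians will be blinded to the group assignment". The Blinding section says that study personnel, participants, physicians and those handling the drug "will be unaware of the group and treatment type until the study is completed".
- **When the code is opened.** The same Blinding section says: "Unblinding occurred if a participant have a serious adverse event during the course of the study or require emergency care in an emergency situation". It continues: "Once unblinded, the participant will be withdrawn from the study and the investigator will report the reason to the examiner within 24 h".
- **What counts as an endpoint event.** Secondary outcome indicators, item 4, lists "the rate of endpoint events (acute exacerbation rehospitalization of CHF, cardiac death and all-cause death" and leaves the list open. Table 3 gives one row for clinical endpoint events, analysed by log-rank test.
- **Who records the events.** Under Adverse events, for a serious event, "the investigator will fill out a serious adverse reaction form to record the time of occurrence, severity, duration, measures taken and regression". Under Withdrawal criteria, the investigator is to "follow up on the occurrence of the endpoint event in the withdrawing patient".
- **Link to stopping.** Termination criteria lists "5) an endpoint event" as its last item.

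**The concern.** The events most likely to open the code are also events that the efficacy comparison counts. Whether an admission was an acute exacerbation of heart failure or something else is a judgement. If it is made after the arm is known, that part of the log-rank comparison loses the protection of blinding, and an expectation of benefit could shift arguable admissions out of the XBP count or into the placebo count.

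This matters for this trial in particular. The Discussion criticises earlier XBP studies for lacking double blinding and presents the present design as the remedy. Taken at face value, the unblinding rule brings that weakness back for the judged part of the clinical-event outcome.

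**Working it through.** **Step 1. Do the stated rules conflict?** The blinding statements run to the end of the study. The unblinding sentence names two triggers, a serious adverse event and emergency care. The first carries no condition such as need for patient management. A code-break for individual emergencies is a normal exception to blinding. A rule that covers every serious adverse event is wider than that, and it cannot be squared with physicians and staff staying unaware until completion.

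**Step 2. Do endpoint events meet the trigger?** The article does not define a serious adverse event. In the usual meaning, admission to hospital and death both qualify. An acute-exacerbation admission would often also meet the emergency-care trigger. This is an inference from common usage, not a quotation.

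**Step 3. Who makes the judgement?** After unblinding the patient is withdrawn, and it is the investigator who reports the reason, completes the serious-event form and follows up endpoint events in withdrawn patients. The article does not say who receives the code, or whether the event is classified before or after it is opened.

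**Step 4. Which results are exposed?**

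| Result | Needs a judged cause? | Exposed by this route? |
|---|---|---|
| Readmission for acute exacerbation | Yes | Yes |
| Cardiac death, if analysed separately | Yes | Yes |
| All-cause death | No | No |
| Counts of serious adverse events (Table 3) | Seriousness is recognised before the code opens | Not materially |
| NT-proBNP responder (primary) | No, laboratory value | Not by classification |

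**Step 5. How large could it be?** The article gives no expected event rate, so nothing here can be reproduced from it. If 5% to 20% of the 284 patients had a triggering event (an assumption), 284 × 0.05 = 14 to 284 × 0.20 = 57 codes would be opened.

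For the effect on the test, take 142 per arm (Sample size) and no true effect. The remaining inputs are assumptions: a share *a* of patients has a possible heart-failure admission within 24 weeks, a share *s* of these has an arguable cause, and assessors who know the arm count 25% of the arguable cases under XBP and 75% under placebo. Blinded assessors would count 50% in both arms.

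- Counted proportion under XBP: x = a(1 − s + 0.25s). Under placebo: p = a(1 − s + 0.75s).
- Apparent hazard ratio with exponential times: ln(1 − x) / ln(1 − p).
- Approximate log-rank shift: |ln HR| × √(D/4), with D = 142(x + p). Two-sided rejection is read from the normal distribution at ±1.96.

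| a, s | x | p | D | HR | Shift | Rejection, formula | Rejection, simulated (6,000 trials) | Simulated, blinded |
|---|---|---|---|---|---|---|---|---|
| 10%, 20% | 0.085 | 0.095 | 25.6 | 0.89 | 0.29 | 6.0% | 6.3% | 5.0% |
| 20%, 40% | 0.14 | 0.18 | 45.4 | 0.76 | 0.92 | 15.2% | 14.8% | 5.2% |
| 30%, 40% | 0.21 | 0.27 | 68.2 | 0.75 | 1.19 | 22.2% | 22.0% | 4.6% |

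In the first row about four-fifths of rejections favour XBP (4.8% of 6.0%). In the other two rows almost all do.

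**The case against.** The strongest reply is that this is a condensed article. Code-break steps, the recipient of the code and the way events are classified commonly sit in the full protocol, which is not shown. The Abstract also names outcome assessors separately from study physicians, so a separate blinded classifier may exist. That stands as far as it goes: the text shows that events can be classified with knowledge of the arm, not that they will be. It does not remove the point, because the fault is in a rule the article states, and that rule contradicts the article's own blinding statements.

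Three stronger readings are tempting and should not be made.

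- **Every endpoint event unblinds its own case.** The article gives no definition of a serious adverse event, leaves the endpoint list open, and keeps efficacy events and adverse events apart in Table 2. The overlap is likely, but it is inferred.
- **Death is compromised as well.** All-cause death is on the list, so if the listed events are pooled every death counts whatever its cause. Only a separate cardiac-death analysis would be exposed, and none is stated.
- **The safety comparison becomes open-label.** A serious event has to be recognised as serious before it can open the code, and Table 3 compares only numbers and percentages. Severity is recorded on the form, but no listed comparison uses it.

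It is also fair to object that the illustration assumes every arguable case is unblinded before it is classified, models admissions only (deaths would dilute the effect), and uses all 142 per arm although 20% missed visits are expected. Its lowest setting is close to the nominal 5%.

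**Conclusion.** The point holds in a limited form. The unblinding rule, as written, is not restricted to cases where care needs the code and conflicts with the blinding statements in the same section and in the Abstract. It leaves the cause of readmission, and of death if cardiac death is analysed on its own, open to classification by someone who knows the arm. This is one judged component of one secondary outcome. The primary outcome, all-cause death and the serious-event counts are not materially affected by this route.

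The conclusion rests on the usual meaning of a serious adverse event and on the article's silence about the order of classification and unblinding. The size of any bias cannot be derived from the documents. The 6% to 22% range shows what assumed rates and an assumed 25%/75% lean would do; it is not an estimate for this trial. The change is still worth making because it is cheap.

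**What to change.** 1. Reconcile the Abstract, Withdrawal criteria, Blinding, Secondary outcome indicators and Adverse events sections so that they describe one consistent arrangement. When the code is opened for patient care stays with the investigators; no rule is proposed here.
2. Require that the date and category of each endpoint event (heart-failure exacerbation or other admission; cardiac or other death) be entered in the CRF before the arm is disclosed to the person classifying it.
3. Flag every event classified after unblinding, and report the number by arm.
4. Add a log-rank sensitivity analysis using all-cause admission or death, which needs no judgement of cause.

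Cost: one or two sentences in the protocol, a date and time field on the CRF, a short recording step for the site at each event, and one extra analysis. The all-cause analysis will also count admissions unrelated to heart failure, which may dilute a real effect, so it should support the main comparison and not replace it.

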### Statistical analysis methods

All statistical tests will be performed using a two-sided test, and a *p* value less than or equal to 0.05 will be considered statistically significant for the difference tested. Dichotomous indicators will be used to describe the number of cases and percentages of each category. Quantitative indicators conforming to normal distribution will be expressed as the “mean ± standard deviation” and skewed data will be described as the median, lower quartile (Q1), and upper quartile (Q3). Comparisons between the two general groups will be analyzed using appropriate methods depending on the type of indicator. Paired *t* test or Wilcoxon rank sum test will be used for comparison between groups for quantitative data, chi-square test or Fisher exact probability method for categorical data, and Wilcoxon rank sum test or CMH test for rank data. The specific applicable statistical methods for each outcome indicator are shown in Table 3.

**TABLE 3 T3:** Outcomes and methods of analyses.

Outcome/variable	Hypothesis	Measures	Methods of analyses
Baseline balance test		Quantitative outcomes (age, temperature, heart rate, respiratory rate, and blood pressure)	*t*-test/Wilcoxon rank-sum test
		Qualitative outcomes (sex, marriage, and previous treatment)	Chi-squared test/Fisher’s exact test/rank-sum test
Primary outcome			
Percent and cases of NT-proBNP decreased ≥30%	decrease occurred		Chi-square test/Fisher’s exact test
Secondary outcome			
NYHA class	decrease occurred		Wilcoxon rank-sum test
6MWT	increase occurred		*t*-test/Wilcoxon rank-sum test
MLHFQ score	decrease occurred	Questionnaire	*t*-test/Wilcoxon rank-sum test
Clinical-endpoint events	decrease occurred	Clinical-endpoint event rate	Log-rank test
NT-proBNP	decrease occurred		*t*-test/Wilcoxon rank-sum test
Echocardiographic parameters	Improvement occurred	LVEF, LVEDD, LVESD	*t*-test/Wilcoxon rank-sum test
TCM symptom scores	decrease occurred	Disappearing rate of main symptoms	Chi-square test/Fisher’s exact test
Safety outcomes			
AEs, SAE		Percent and cases of AEs and SAEs	Chi-square test/Fisher’s exact test

NYHA, New York heart association; 6MWT, 6-min walk distance; MLHFQ, Minnesota living with heart failure questionnaire; LVEF, left ventricular ejection fraction; LVEDD, left ventricular end-diastolic diameter; LVESD, left ventricular end-systolic diameter; AE, adverse event; SAE, serious adverse events; TCM, traditional Chinese medicine.

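### The TCM score formula has the opposite sign to the reduction its response classes need, the top two classes overlap, and Table 3 lists a different TCM measure

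*Protocol article*

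**What the plan says.** All of this concerns the seventh secondary outcome in the protocol article. Under Secondary outcome indicators:

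- The outcome is introduced as a symptom measure: "TCM symptom scores (Supplementary material 1) will be used to quantify the symptoms".
- A comparison of scores is planned: "Differences in TCM symptom scores between groups at baseline and week 4, week 8, week 12 and week 24 post-treatment will be compared".
- Three response classes follow, with cut-offs in per cent. The lowest is "ineffective: no significant improvement or even worsening of symptoms and signs, and a reduction in symptom score <30", the middle is "effective: improvement of symptoms and signs, and a reduction in symptom score ≥30" and the top is "significant effect: significant improvement of symptoms and signs, and a reduction of syndrome score ≥70".
- The next sentence gives the formula, "TCM symptom scores = [(posttherapy score - pretherapy score)/pretherapy score", multiplied by 100%.

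Under Statistical analysis methods, the TCM row of Table 3 gives the measure as "Disappearing rate of main symptoms", the hypothesis as a decrease, and the test as chi-square or Fisher's exact. The text above the table assigns t or Wilcoxon tests to quantitative data and Wilcoxon or CMH tests to rank data.

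**The concern.** The classes are cut on a positive reduction, while the formula printed with them is a signed change that is negative for improvement. A programmer who takes the formula as the derivation of the quantity being cut would get wrong or missing classes for the patients who respond best.

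Separately, the outcomes section sets up two TCM variables (the score compared between groups, and the ordered three-class response) and Table 3 sets up a third (a disappearance rate). With three candidate variables and no text linking them, the choice of reported result stays open. The protocol's own Discussion criticises earlier studies of this drug for the risk of selective outcome reporting, so this is worth closing.

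**Working it through.** **Inputs.** The formula and the 30% and 70% cut-offs come from Secondary outcome indicators. The baseline score of 20 is an illustrative assumption; the percentages do not depend on it. The protocol states no result here to reproduce.

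**Step 1: sign.** Printed formula: (post - pre)/pre × 100%. Reduction as the classes need it: (pre - post)/pre × 100%. One is the negative of the other.

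| Post score (pre = 20) | Printed formula | Class by number alone | Reduction | Class by number alone |
|---|---|---|---|---|
| 4 | (4-20)/20 = -80% | ineffective | +80% | significant effect |
| 6 | -70% | ineffective | +70% | significant effect |
| 10 | -50% | ineffective | +50% | effective |
| 14 | -30% | ineffective | +30% | effective |
| 16 | -20% | ineffective | +20% | ineffective |
| 24 | +20% | ineffective | -20% | ineffective |
| 26 | +30% | effective | -30% | ineffective |
| 34 | +70% | significant effect | -70% | ineffective |
| 40 | (40-20)/20 = +100% | significant effect | -100% | ineffective |

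For the table, a value of 70% or more is given the top class. The two versions agree for falls and rises of less than 30% and differ from 30% upwards in either direction.

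**Step 2: add the symptoms-and-signs condition.** Each class joins its numeric cut-off to a clinical statement with *and*. Keep the printed formula and apply both parts:

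- Post score 4, symptoms significantly improved: -80% fails the numeric part of the middle and top classes. It meets the numeric part of the lowest class but fails its clinical part. No class applies.
- Post score 40, symptoms worse: +100% meets the numeric parts of the middle and top classes but fails their clinical parts. It fails the numeric part of the lowest class. Again no class applies.

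So under the full criteria the printed formula leaves such patients unclassified; it does not swap them.

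**Step 3: label.** The formula is named as the TCM symptom score, but the same section compares that score between groups at baseline, when no post-therapy score exists. One term therefore carries two meanings.

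**Step 4: overlap.** The middle class is a reduction of at least 30% with no ceiling; the top class is at least 70%. An 80% reduction meets both numeric conditions, and correcting the sign does not change that.

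**Step 5: Table 3 against the outcomes section.**

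- *Score compared between groups:* quantitative, so the protocol's own rule gives t or Wilcoxon. The questionnaire row (MLHFQ) of Table 3 follows that rule; the TCM row does not.
- *Three-class response:* ordered, so the protocol's own rule gives Wilcoxon or CMH. The TCM row does not list it.
- *Disappearance rate:* a proportion, so chi-square or Fisher fits, but it is neither of the two variables above. The row's hypothesis of a decrease suits a score; for a disappearance rate, benefit would be an increase.

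**The case against.** The best defence is that no careful reader would be misled. The formula is an ordinary signed percent change, -75% is plainly a 75% reduction, the criteria say *reduction* in words, and Table 3 expects a decrease. The classes form an ascending list, so an 80% reduction would naturally go to the highest class met. Much of this stands: the intended direction is clear. It does not make the printed expression the quantity that the cut-offs need, nor does it justify the label.

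Three stronger readings might be inferred, and the document does not support them.

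- *Every improving patient is scored ineffective, and patients who worsen by 70% or more are scored as a significant effect.* This requires the formula value to be used as the reduction and the symptoms-and-signs condition to be ignored. Even then, improvers of less than 30% land in the lowest class under either version, so not all improvers are misclassified.
- *The disappearance rate is defined nowhere.* The outcome refers to Supplementary material 1, which is not shown, and a statistical analysis plan may exist. Either could define it. A definition there would still not make Table 3 match the outcomes section.
- *The score and the three-class response have no analysis at all.* The outcomes section says scores will be compared, and the general methods text gives test families for quantitative and rank data. The fault is a mismatch in Table 3, not silence.

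**Conclusion.** The point holds in a limited form. The formula gives the negative of the reduction that the classes use and is mislabelled as the score. Used against the cut-offs, it makes every fall of 30% or more fail the numeric part of both response classes; with the clinical condition applied, a patient with such a fall and significantly improved symptoms fits no class. The middle class numerically contains the top class. Table 3's TCM row does not analyse either variable defined in the outcomes section.

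The consequence for classification rests on the assumption that the printed formula is what gets programmed as the reduction. The overlap and the Table 3 mismatch need no such assumption. How many patients would be affected cannot be derived, because the document gives no expected distribution of TCM scores. The effect is confined to one secondary outcome: the primary outcome and the sample size rest on NT-proBNP response and are unchanged.

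**What to change.** Before unblinding:

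1. Replace the formula with percent reduction = (pre - post)/pre × 100%, and label it as percent reduction in TCM score, not as the score.
2. Make the numeric bands mutually exclusive: below 30%, 30% to below 70%, and 70% or more.
3. In Table 3, list the between-group comparison of TCM scores (t-test or Wilcoxon, ideally adjusted for the baseline score) and the ordered three-class response (Wilcoxon or CMH, as the protocol already prescribes for rank data). Keep the disappearance rate only as an additional measure with its own definition and the right direction of benefit.

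Baseline adjustment is a recommendation, not the correction of an error. The cost is a few lines of text and changes to the TCM entry in Table 3. No new data are needed, since Table 2 already schedules the TCM score at baseline and at weeks 4, 8, 12 and 24.
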